**1.3 Animal Pharmacokinetic Studies**

The pharmacokinetics of SD rats and crab-eating macaques after a single intravenous injection or IV infusion of RC48-ADC was assayed by ELISA and LC/MS/MS; ^125^I isotopic labeling assay of RC48-ADC was used to study the tissue distribution and excretion of RC48-ADC in nude mice bearing tumors. The ^125^I isotopic labeling assay of RC48-ADC was also used to perform biliary excretion studies and plasma binding rates in SD rats. The free MMAE was determined by LC-MS/MS and the stability of RC48-ADC incubated in vitro with different species (human, monkey, dog, and rat) at 37°C for 21 days was observed.

**1.3.1 Pharmacokinetics in Rats**

(1) ADC and TAb showed linear pharmacokinetics in rats within the experimental dose range (4, 8 and 16 mg/kg); MMAE showed linearity in the dose range of 4 and 8 mg/kg and non-linear pharmacokinetics when the dose was increased to 16 mg/kg.

(2) After a single intravenous injection of RC48-ADC in rats, serum concentration curves of ADC and TAb of the same animal were gradually separated over time. The levels of TAb and ADC were similar at the early stage of drug administration, but the concentration difference increased gradually over time between the two drugs.

(3) Compared with the same dose of RC48-ADC intravenously injected in rats, the peak concentration of Tab and the exposure level were similar for the combined MMAE and nude antibody group with a consistent half-life, and there was no statistical difference in pharmacokinetic parameters.

(4) The exposure level of MMAEin the ADC group is far lower than that of the combined MMAE and nude antibody at the same dose, which is about one thousandth.

**1.3.2 Pharmacokinetics of Crab-Eating Macaques**

(1) ADC, TAb, and MMAE showed nonlinear pharmacokinetics in crab-eating macaques within the experimental dose range (2, 4 and 8 mg/kg), and the systemic clearance gradually decreased with increasing doses.

(2) After a single intravenous infusion at different doses of RC48-ADC in cynomolgus monkeys, serum concentration and pharmacokinetic parameters of ADC and TAb were similar, with no statistical difference.

(3) The TAb concentration of the nude antibody group was higher than that of the RC48-ADC group

For 4 mg/kg RC48-ADC and 4 mg/kg RC48 nude antibody + 0.08 mg/kg MMAE control group, all pharmacokinetic parameters regarding total antibody except MRT were not statistically different. The plasma concentration of the nude antibody group was higher than that of the RC48-ADC group.

(4) The MMAE exposure level of RC48-ADC was much lower than that of the combined MMAE and nude antibody group at the same dose. The systemic exposure and maximum toxic concentration of RC48-ADC were about 1/5 (18.18%) and 1/310 (0.32%) of those of the latter respectively, suggesting that the free MMAEs detached from RC48-ADC were maintained at a relatively low exposure level in crab-eating macaques' blood.

After a single intravenous injection of combined RC48 nude antibody + MMAE (4+0.08 mg/kg) in the control group, the plasma concentration peaked instantaneously. The peak concentration and plasma exposure of free MMAE after 4 mg/kg RC48-ADC administration were approximately 0.32% and 18.18% of those of the control group at the same dose. This result suggested that the cytotoxic pentapeptide MMAE conjugated to RC48-ADC was stable in the blood, and the systemic exposure of free MMAE within 14 days after a single intravenous infusion in crab-eating macaques was less than 20% of the amount of its conjugate. The maximum toxic concentration was reduced by more than 300 folds, theoretically reducing the systemic toxicity caused by MMAE.

**1.3.3 Tissue Distribution Characteristics of HER2-Positive Tumor-Bearing Mice Presents with Targeting to Tumor Tissues**

Tissue distribution characteristics in HER2-positive tumor-bearing mice have demonstrated the drug's targeting ability to tumor tissues and inability to cross the blood brain barrier. After intravenous injection of 125I-RC48-ADC (12 mg/kg), the exposure level (AUC) of TCA precipitable fraction in tissues was ranked in descending order as follows: serum, tumor, liver, adrenal gland, kidney, lung, urine, submandibular gland, gonads, lymph nodes, spleen, heart, bladder, small intestine, fat, muscle, pancreas, eyeballs, feces, intestinal contents, brain and bone marrow.

**1.3.4 The drug is excreted predominantly via urine with a small amount excreted via feces in HER2-positive tumor-bearing mice**

**Excretion characteristics:** Predominantly excreted via urine, with a small amount excreted via feces and bile. After intravenous injection of ^125^I-RC48-ADC (12 mg/kg) in tumor-bearing mice, slow radioactive excretion rate was observed, with 75.64% ± 2.80% and 0.90% ± 0.13% of injected radioactive dose being excreted in urine and feces at 336 h. The radioactive excretion in urine and feces totaled 76.53% ± 2.80% of the administered radioactive dose. SEC-HPLC assay showed that metabolites in urine were small molecular degradation products without parent drug. Cumulative excretion ratio in urine accounted for 0.17%±0.06% of administered radioactive dose 24 h after intravenous injection of ^125^I-RC48-ADC (8 mg/kg) in rats.

**1.3.5 Inability to bind to plasma proteins in tumor-bearing mice**

The chromatographic analysis of blood samples after administration in tumor-bearing mice revealed that the drug was predominantly present in the form of ^125^I-RC48-ADC, not binding to plasma proteins.

**1.3.6 Stability test of RC48-ADC in plasma in vitro**

Results showed that: (1) RC48-ADC was stable in plasma of various animal species, with less than 1.8% of free MMAE present after 21-day storage at 37°C. That was comparable to SGN-35, whose MMAE dissociation rate was approximately 2% under the same condition. (2) RC48-ADC was stable in the plasma of different animal species with a descending stability order as follows: monkey > dog > human > rat. This result was consistent with the stability of SGN-35 in plasma.

**1.4 Safety Evaluation Study in Animals**

According to regulations and guidelines concerning drug evaluation in China, following studies were carried out on RC48-ADC under GLP conditions: tissue-binding study with normal tissues in humans, cynomolgus monkeys and SD rats; general pharmacological study in cynomolgus monkeys and SD rats; acute toxicity study with single intravenous infusions in cynomolgus monkeys and SD rats; chronic toxicity study with repeated intravenous infusions for 12 weeks followed by a recovery period of 6 weeks in SD rats and cynomolgus monkeys; special toxicity (hemolysis) study; active systemic anaphylaxis test in guinea pigs; and immunotoxicity and/or immunogenicity study, local irritation study and toxicokinetic study in combination with chronic toxicity tests. Major results are as follows:

**Tissue cross-reactivity study** showed that the RC48-ADC and its nude antibody exhibited similar cross reactivity with normal human and cynomolgus monkey tissues. Both of them binded specifically to normal tissues of bladder, skin, mammary gland, pancreas, placenta, kidney, prostate, ureter, fallopian tube and stomach in humans and normal tissues of bladder, mammary gland, pancreas, liver, lung, kidney, prostate and ureter in cynomolgus monkeys. RC48-ADC showed no specific binding to normal tissues in SD rat, while the control RC48 nude antibody bound specifically to normal gastric tissues in SD rats. It can be seen from the tissue cross-reactivity study that cynomolgus monkeys, rather than rats, are the relevant animal for RC48-ADC administration in humans.

**General pharmacological study** demonstrated that RC48-ADC and its constituents (RC48 nude antibody and MMAE) have no significant effects on mental and nervous system of SD rats, and RC48-ADC and MMAE have no significant effects on cardiovascular system and respiration of awake monkeys monitored remotely.

**Acute toxicity study** showed that MTD was measured to be 24 mg/kg, 40 mg/kg and 0.4 mg/kg in SD rats and 10 mg/kg, 27 mg/kg and 0.12 mg/kg in cynomolgus monkeys after single intravenous injections of RC48-ADC, RC48 nude antibody and MMAE, respectively.

**Chronic toxicity study** showed that MTD was measured to be 12 mg/kg, 24 mg/kg (Q2W×4) and 0.2 mg/kg in SD rats and 10 mg/kg, 12 mg/kg and 0.12 mg/kg in cynomolgus monkeys, after repeated intravenous infusions Q2W of RC48-ADC, RC48 nude antibody and MMAE for 7 times in total, respectively. Major toxic reactions included immunosuppression and hematopoietic inhibition in both rats and monkeys, and digestive tract injuries and testicular and epididymis atrophies were observed in rats. RC48-ADC and MMAE have basically the same toxic reactions.

**Allergy study** showed positive active systemic anaphylaxis for RC48-ADC and RC48 nude antibody, and negative anaphylaxis for the pentapeptide constituent MMAE in guinea pigs.

**Immunotoxicity and/or immunogenicity study** demonstrated the immunosuppression of RC48-ADC. After repeated intravenous infusions, incidence of immunogenicity (ADA) increased with dose in SD rats, and decreased with dose in cynomolgus monkeys. This may be due to the immunosuppression in cynomolgus monkeys.

**Special toxicity study** demonstrated by local irritation tests that no irritative reaction was found at injection sites after repeated Q2W intravenous infusions of RC48-ADC in cynomolgus monkeys at 0.6-2.4 mg/mL and rats at 1.2-4.8 mg/mL. In vitro hemolysis tests showed no hemolysis or agglutination in response to the administration of RC48-ADC at 1.8mg/mL.

Results of safety evaluation tests suggested that cynomolgus monkeys are the relevant animal for simulate administration of RC48-ADC in humans. RC48-ADC and MMAE induced basically the same toxic reactions in cynomolgus monkeys and SD rats, wherein the major toxic reactions included immunosuppression and hematopoietic inhibition. No administration-related irritative reaction was found at injection sites. RC48-ADC group exhibited a less severe toxic reaction than MMAE group with an equal dose of MMAE. No significant toxic reactions were found in RC48 nude antibody group.

**1.5 Preliminary Study Results**

As of July 1, 2017, a total of 25 valid subjects have been enrolled in the study. Dose escalation has reached 2.5 mg/kg, with DLT of Grade 4 neutropenia occurring in 2 cases at the dose of 2.5 mg/kg. Drug-related adverse events (≥5%) included leukopenia (14%), neutropenia (9%), decreased hemoglobin (7%) and numbness (6%). Adverse events that led to changes in medication (including dose reduction, dosing suspension and medication termination) were leukopenia, neutropenia and numbness of hands and feet. All symptoms were resolved after dose discontinuation or symptomatic treatment.

As of July 1, 2017, efficacy evaluation has been conducted on 19 subjects, among which 3 were evaluated as partial response (PR), 8 were stable disease (SD), and 8 were progressive disease (PD). The duration time for administration is up to 238 days.

Pharmacokinetic study showed that half-lives of RC48-ADC in the groups of 1.0 mg/kg, 2.0mg/kg and 2.5mg/kg were 16.2±9.5 h, 34.4±13.7 h and 49.0±27.4 h, respectively. Exposure level AUC_0-∞_ increased with dose. No anti-drug antibody was detected so far.

**2 Study Objectives**

**Primary objectives:** To determine the maximum tolerated dose (MTD) and safety of RC48-ADC in patients with HER2-positive advanced malignant solid tumors, and to determine the recommended dose in the Phase II clinical trial.

**Secondary objectives:** To investigate the pharmacokinetic (PK) characteristics of RC48-ADC in patients with HER2-positive advanced malignant solid tumors, and to initially observe the clinical efficacy of RC48-ADC in the treatment of HER2-positive advanced malignant solid tumors.

**Exploratory objectives:** To analyze the drug-to-antibody ratio (DAR) of RC48-ADC over time in patients with advanced HER2-positive malignant solid tumors.

**3 Study Design**

It is expected to set up 9 dose groups to conduct an open-label, dose-escalation study. Patients with HER2-positive solid tumors are enrolled.

The doses are proposed to be escalated to 0.1 mg/kg, 0.5 mg/kg, 1.0 mg/kg, 1.5 mg/kg, 2.0 mg/kg, 2.5 mg/kg, 3.0 mg/kg, 3.5 mg/kg and 4.0 mg/kg.

If a dose has passed the safety observations in another Phase I clinical trial (at the Cancer Hospital, Chinese Academy of Medical Sciences), investigators and sponsors may meet to discuss and adjust the dose increment in dose escalation trial, or skip this dose and proceed directly to the next dose according to the corresponding results, in order to reduce the patient's exposure to ineffective doses.

During the trial, the dose increment and the maximum dose can be adjusted based on actual results after consultation between the investigators and sponsor.

The first dose (0.1 mg/kg) is given to 1 subject to collect pharmacokinetic data of a single dose. After safety observations, the patient can continue with trials of the following dose levels on a voluntary basis without additional collection of pharmacokinetic data (this scheme is suitable to all subsequent subjects to ensure their benefits).

The second dose (0.5 mg/kg) group enrolls another subject. Pharmacokinetic data of a single dose are collected for this patient after first dosing. Dosing interval (Q1W, Q2W or Q3W) will be determined by the investigators and sponsor based on the data obtained from the 2 patients. Q2W was tentatively selected at a meeting on Jan. 26, 2016. Q2W dosing means 1 treatment cycle includes 2 doses.

Repeated doses are given to subjects from the second dose (0.5 mg/kg) forward to collect pharmacokinetic data of repeated doses. Pharmacokinetic data are collected before and after each of 4 doses for one patient, no matter what dosing interval is used.

Subjects are enrolled in the traditional 3+3 mode from the third dose (1.0 mg/kg) forward. At first, 3 qualified subjects are enrolled into the 1.0 mg/kg group. If no DLT is observed in the 3 subjects during the DLT evaluation period, the dose is escalated to the next level; if DLT occurs in 1/3 of the subjects (1 case) in the 1.0 mg/kg group, another 3 subjects should be added. If no DLT is observed in the additional 3 subjects, trials at the next dose level may be started; if DLT occurs in 1 or more of the 3 additional subjects, or in 2 or more of the 6 subjects in total, the dose escalation should be discontinued. Trials in the same manner are performed with dose escalation until the maximum tolerated dose (MTD) and recommended phase Ⅱ dose (RP2D) are determined.

[figure not shown]

All subjects are evaluated as CR, PR or SD after the 4th administration. If the patients are willing to do so, and the investigator determines that continued administration will be of benefit to the patients, patients can enter the extended test in which treatment is continued until the disease progresses, the toxicity become intolerable, the patients withdraw consent or the investigator determines that the medication must be discontinued.

**Dose-limiting toxicity (DLT)** refers to the following toxic reactions observed in the DLT evaluation window (observation period of Day 1-21 after the first dose) that are considered related to RC48-ADC treatment by the investigators or sponsor, wherein the grading is based on the 5-level system of the CTCAE v4.0:

- Grade 4 neutropenia.
- Neutropenic fever (defined as absolute neutrophil count ^[^ANC] < 1000/mm3 accompanied by a fever higher than 38.3 °C or a fever above 38 °C that persists for more than 1 h).
- Grade 3 neutropenia with confirmed infections.
- Grade 3 thrombocytopenia with bleeding tendency.
- Grade 4 thrombocytopenia.
- Non-hematologic toxicity of Grade 3 or higher after supportive care. Except for nausea, vomiting and hair loss.
- Renal toxicity ≥ Grade 3.
- Neurological toxicities ≥ Level 2 that persist until the next administration.
- Cardiac toxicity ≥ Grade 2.
- Hepatic transaminases reach grade 2 at baseline, with a level ≥10×ULN.

If DLT appears in the subjects, treatment of RC48-ADC should be discontinued first, and adverse reactions should be dealt with actively until the toxicity returns to ≤ Grade 1. Thereafter, medication should proceed at a decreased dose level (specific doses will be determined by the investigators).

**Maximum Tolerated Dose (MTD)**: The lower dosage next to a dose with which DLT occurs in 2 or more out of 6 patients during the DLT evaluation window.

Dose groups of 3 to 6 subjects were formed starting with the lowest dose set by the protocol:

(1) If none of the 3 subjects develop DLT within the 21-day observation period after the first dose, the next (escalated) dose trial can be performed.

(2) If DLT occurs in 1 of the 3 subjects, the number of subjects in this dose group should be increased to 6: (a) if DLT occurs in 2 or more of these 6 subjects, the next (escalated) dose trial should be terminated; (b) if DLT occurrs in no more than 1 of the 6 patients, the next (escalated) dose trial can be performed.

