**On July 4, 2017, the investigators and sponsor decided to modify the DLT definition based on the current study results:**

**DLT** refers to the following toxic reactions observed in the DLT evaluation window (observation period of Day 1-21 after the first dose) that are considered related to RC48-ADC treatment by the investigators or sponsor, wherein the grading is based on the 5-level system of the CTCAE v4.0:

- Grade 4 neutropenia lasting more than 3 days after symptomatic treatment; or grade 4 neutropenia recurring after recovery to a normal level through symptomatic treatment.
- Neutropenic fever (defined as absolute neutrophil count ^[^ANC] < 1000/mm3 accompanied by a fever higher than 38.3 °C or a fever above 38 °C that persists for more than 1 h).
- Grade 3 neutropenia with confirmed infections.
- Grade 3 thrombocytopenia with bleeding tendency.
- Grade 4 thrombocytopenia.
- Non-hematologic toxicity of Grade 3 or higher after supportive care. Except for nausea, vomiting and hair loss.
- Renal toxicity ≥ Grade 3.
- Neurological toxicities ≥ Level 2 that persist until the next administration.
- Cardiac toxicity ≥ Grade 2.
- Hepatic transaminases reach grade 2 at baseline, with a level ≥10×ULN.

If DLT appears in the subjects, treatment of RC48-ADC should be discontinued first, and adverse reactions should be dealt with actively until the toxicity returns to ≤ Grade 1. Thereafter, medication should proceed at a decreased dose level (specific doses will be determined by the investigators).

**Maximum Tolerated Dose (MTD)**: The lower dosage next to a dose with which DLT occurs in 2 or more out of 6 patients during the DLT evaluation window.

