**Blood Collection for PK During Dose-Escalation Trial:**

Blood collection time points for Q2W administration:

The blood collection points for the first dose (11 blood collection points): before administration (0 h), 0.25 h, at the end of infusion, 1.5 h, 12 h, 24 h, 48 h, 72 h, 120 h, 168 h and 240 h.

For the second dose (1 blood collection point): before administration (336 h).

For the third dose (1 blood collection point): before administration (672 h).

For the fourth dose (12 blood collection points): before administration (1008 h), 0.25 h (1008.25 h), at the end of infusion, 1.5 h (1009.5 h), 12 h (1020 h), 24 h (1032 h), 48 h (1056 h), 72 h (1080 h), 120 h (1128 h), 168 h (1176 h), 240 h (1248 h) and 336 h (1344 h).

Blood samples are collected at these 25 time points to detect serum ADC, TAb and free MMAE, with a collection volume of 2 mL each time.

Blood collection points for immunogenicity (ADA) assays: Serum anti-ADC antibodies are detected before the first, second, third and fourth doses, and 336 hours after the fourth dose (5 collection points), with 1 mL of blood volume for each sample.

Blood collection time points for Q3W administration:

The blood collection points for the first dose (11 blood collection points): before administration (0 h), 0.25 h, at the end of infusion, 1.5 h, 12 h, 24 h, 48 h, 72 h, 120 h, 168 h and 240 h.

For the second dose (1 blood collection point): before administration (504 h).

For the third dose (12 blood collection points): before administration (1008 h), 0.25 h (1008.25 h), at the end of infusion, 1.5 h (1009.5 h), 12 h (1020 h), 24 h (1032 h), 48 h (1056 h), 72 h (1080 h), 120 h (1128 h), 168 h (1176 h), 336 h (1344 h) and 504 h (1512 h).

Blood samples are collected at these 24 time points to detect serum ADC, TAb and free MMAE, with a collection volume of 2 mL each time.

Blood collection points for immunogenicity (ADA) assays: Serum anti-ADC antibodies were detected before the first, second and third doses, and 504 h after the third dose (4 collection points), with 1 mL of blood volume for each sample.

Blood collection time points for QW administration:

The blood collection points for the first dose (9 blood collection points): before administration (0 h), 0.25 h, at the end of infusion, 1.5 h, 12 h, 24 h, 48 h, 72 h and 120 h.

For the second dose (1 blood collection point): before administration (168 h).

For the third dose (1 blood collection point): before administration (336 h).

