For the fourth dose (10 blood collection points): before administration (504 h), 0.25 h (504.25 h), at the end of infusion, 1.5 h (505.5 h), 12 h (516 h), 24 h (528 h), 48 h (552 h), 72 h (576 h), 120 h (624 h) and 168 h (672 h).

Blood collection points for immunogenicity (ADA) assays: Serum anti-ADC antibodies are detected before the first, second, third and fourth doses, and 336 hours after the fourth dose (5 collection points), with 1 mL of blood volume for each sample.

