If there occurs a QTcF interval > 500 ms or increasing by > 60 ms relative of the baseline or grade III atrioventricular block during trial, then the trial medication should be suspended. The investigators will decide whether or not to continue medication after defining its cause.

In a non-DLT observation cycle, if any clinically significant AE occurring in one subject is judged by the investigators to be potentially, probably or definitely relevant to the study drug, and this AE is likely to continue or be potentially aggravated in the next scheduled dosing, then the investigators may postpone dosing or stop one dose of the study drug, the delay may last for up to 21 days or dose level may be lowered by 1 or 2.

The following provisions apply to toxic reaction occurring beyond DLT evaluation window.

Non-Hematological Toxicity

If any grade 4 non-hematological toxicity occurs in a patient postdose, or there occurs any important injury of organs such as lungs, cardiovascular system, liver and kidneys, then treatment of the patient should be immediately terminated.

If a patient gets any clinical benefit after treatment, but exhibits over grade 3 non-hematological toxicity (except hair loss, nausea, and emesis) and can be recovered to normal, grade 1 or baseline level in 14 days after the optimal supportive therapy, then one dose reduction is allowed. The specific dose shall be determined by the investigators and the sponsor through mutual negotiation (it may be a previous dose subjected to safety assessment or an arbitrary dose previously assessed). If the subject fails to be recovered to normal, grade 1 or baseline level in 14 days, then the investigators and the sponsor will discuss and decide whether or not to terminate the study treatment. If a toxic reaction occurs at the first dose level, then the dose can be reduced to 50%. Subsequent dose escalation trial will be adjusted by the investigators and the sponsor through negotiation.

Hematological Toxicity

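### Move-up is not limited to dose levels that have passed 3+3, and the DLT window is not said to restart there, so a DLT-type event in a moved-up subject need not count

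*Protocol*

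**What the plan says.** Section 3 (Study Design) describes the 0.1 mg/kg subject first. After safety observations, "the patient can continue with trials of the following dose levels on a voluntary basis without additional collection of pharmacokinetic data". A parenthesis widens this: "this scheme is suitable to all subsequent subjects to ensure their benefits". Neither sentence says what state the higher level must have reached.

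The escalation rule in the same section opens the next level on this condition: "If none of the 3 subjects develop DLT within the 21-day observation period after the first dose". With one DLT in three, the group grows to six, and escalation stops at two or more of six. The MTD is the dose below the one where that happens.

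Both DLT definitions, including the one of July 4, 2017, count toxicities "observed in the DLT evaluation window (observation period of Day 1-21 after the first dose". No text says that the window starts again when a subject changes level, or whether a moved-up subject takes one of the 3-6 places.

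Section 7, item (8), covers later toxicity: "The following provisions apply to toxic reaction occurring beyond DLT evaluation window". What follows is delay, reduction or stopping for the individual subject. One sentence there, in the non-hematological part, reaches the escalation itself: "Subsequent dose escalation trial will be adjusted by the investigators and the sponsor through negotiation".

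**The concern.** MTD, safety and the recommended Phase II dose are primary objectives, and the 3+3 count is the only formal rule that produces the MTD. If a subject from the level below joins a level that is still being evaluated, that subject's first dose lies more than 21 days back. Taken literally, Grade 4 neutropenia that would have been a DLT in a new subject then falls under individual dose modification. With 0/3 DLTs in new subjects and 2/2 DLT-type events in moved-up subjects, the written rule would still open the next level.

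The permission is still in force. Section 18 continues Q2W 3+3 escalation to 3.0, 3.5 and 4.0 mg/kg and starts a QW 3+3 escalation at 1.25 and then 1.5 mg/kg.

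**Working it through.** The protocol states no figure on this point, so there is none to reproduce. Three checks follow.

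**1. Text.**
- Condition for moving up: safety observations only (Section 3). This reads as the subject's own observation at the current level.
- Condition for opening a level: the level below has passed (Section 3). So a moved-up subject enters an opened level, but not necessarily one that has passed.
- Events counted: DLTs in days 1-21 after the first dose, among the 3-6 subjects of the group.
- Events outside that window: Section 7, item (8).
- Nothing links a moved-up subject to the count.

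**2. When can overlap occur?** Assumptions: the level below is dosed on day 0, enrolment is immediate, and a subject moves up once their own PK sampling is complete. The text requires only safety observations, so an earlier move is possible and would lengthen the overlap.
- End of PK sampling (Section 6): QW 672/24 = day 28; Q2W 1344/24 = day 56.
- The next level opens on day 21. It is decided on day 21 + 21 = 42 with three subjects, or 42 + 21 = 63 with six.

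| Schedule | Three subjects | Six subjects |
| --- | --- | --- |
| QW | 42 - 28 = 14 days | 63 - 28 = 35 days |
| Q2W | none (56 is after 42) | 63 - 56 = 7 days |

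Only QW with six subjects gives a full 21 days. Slow accrual would lengthen every cell.

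**3. How often would it matter?** Assumptions, none from the protocol: DLT rate p = 0.33 in new subjects, r = 0.15-0.20 in n moved-up subjects, independence, and a full window of overlap. Let X ~ Bin(n, r).
- P(0/3) = 0.67³ = 0.3008
- P(1/3, then 0/3) = 3(0.33)(0.67²)(0.67³) = 0.1337
- P(level passes) = 0.3008 + 0.1337 = 0.434

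Count a pass as doubtful when the pooled proportion reaches the protocol's own threshold of 2/6.
- n = 1: the worst pooled results are 1/4 and 2/7, both below 2/6. Probability 0.
- n = 2: X = 2 gives 2/5 or 3/8, both above 2/6; X = 1 gives 1/5 or 2/8, both below.
- n = 3: X = 2 gives 2/6 or 3/9, both at the threshold; X = 1 gives 1/6 or 2/9, both below.

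So for n = 2 and n = 3 the probability is 0.434 × P(X ≥ 2).

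| n | r = 0.15 | r = 0.20 |
| --- | --- | --- |
| 1 | 0 | 0 |
| 2 | 0.434 × 0.0225 = 0.010 | 0.434 × 0.0400 = 0.017 |
| 3 | 0.434 × 0.06075 = 0.026 | 0.434 × 0.1040 = 0.045 |

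Three is an upper case for a cohort of three. In Section 1.5, 11 of 19 evaluated subjects (3 PR, 8 SD) had not progressed. If non-progression is needed to continue, all three qualify with probability (11/19)³ = 0.194.

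Sensitivity: with r = 0.33, the same rate as in new subjects, P(X ≥ 2) is 0.1089 for n = 2 and 0.2548 for n = 3, giving 0.047 and 0.111. The size therefore depends heavily on an input that the protocol does not supply.

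**The case against.** The strongest reply is that the text can be read harmlessly. A level opens only after the one below passes, and every 3+3 subject receives a dose not yet cleared. "First dose" can mean first dose in that dose group, which puts the event inside the window. Section 3 itself uses first and second dose to mean dose levels, so literal reliance on the phrase is fragile. The sentence was written for the single-dose 0.1 mg/kg subject. For later subjects the detailed path is the extended trial after the fourth dose, and no dose increase is described there.

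The exposure is also narrow. A prompt Q2W cohort of three has no overlap on the timing above. Only two QW levels are planned, and after 1.5 mg/kg the sponsor and investigators decide jointly whether to go on, so an uncounted event there cannot open a higher level automatically. Increments can be adjusted on actual results (Section 3), escalation can be stopped (Section 18), and serious adverse events are reported within 24 hours (Section 11.1).

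Most of this stands and limits the size. What remains is that the group-level reading of the window is possible but unstated, that it leaves open whether the subject takes a cohort place, and that no safeguard requires the event to be weighed before a level passes.

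A reader might infer three stronger things:
- That the 3+3 pass probability is inflated. If only new subjects fill the cohorts, it stays at 0.434 under the assumed rate.
- That toxicity has already been missed this way. The protocol does not show that any subject has moved up.
- That every pass with two or more pooled events is improper. That count gives 0.020-0.027, 0.044-0.060 and 0.070-0.097 for one, two and three moved-up subjects, but much of it is 2/7, 2/8 or 2/9, below the 2/6 threshold.

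**Conclusion.** The gap is real but small. On a literal reading, Section 3 lets a subject be added at a level still under 3+3 evaluation without requiring a DLT-type event there to count toward escalation or the MTD. It matters only with overlap: the QW step from 1.25 to 1.5 mg/kg, a cohort expanded to six, or slow accrual.

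Conditional on full overlap and on the assumed rates (0.33 new, 0.15-0.20 moved-up), the chance of a pass at a pooled proportion of 2/6 or more is 0, 0.010-0.017 and 0.026-0.045 for one, two and three moved-up subjects. Most overlaps in the timing table are shorter than 21 days, which would lower these figures; a higher rate in moved-up subjects would raise them. A cheap improvement, worth making because it concerns subject safety and a primary objective.

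**What to change.** Add to Section 3:

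*From 1.0 mg/kg upward (Q2W) and for all QW levels, a subject may move up only to a dose level that has already passed the 3+3 rule; for 0.5 mg/kg, only after its single subject has completed the 21-day observation. Only subjects whose first RC48-ADC dose is at a level count toward its 3-6 places and the MTD rule.*

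The 0.5 mg/kg clause is needed because that level has one subject and no 3+3 evaluation. The two sentences belong together: the second excludes moved-up subjects from the count, which is acceptable only because the first keeps them away until the level has passed.

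Merely defining the window as starting at the first dose at that level would bring the event inside it, but would not settle who fills a cohort place and would still allow dosing at a level under evaluation.

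The cost is amendment wording. Some subjects wait before moving up, and subjects already on study cannot fill cohort places.
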